## Trial design

The study is a non-blinded superiority cRCT conducted in selected areas of the Federal Territory of Kuala Lumpur and Putrajaya, Malaysia. The trial protocol was registered with the ISRCTN registry on 17 April 2020 as ISRCTN81915073.

For the purpose of the trial, a cluster is defined as a locality, i.e. one residential area composed of neighbouring buildings that share the same facilities such as parking lots, food court, groceries store, playground, and community halls.

The trial includes 300 clusters (mean number of buildings per clusters = 4) which were randomly allocated in a 1:1 ratio, to receive either the proactive IVM in addition to the routine vector control activities or the routine vector control activities only (see the “Interventions” section for more details). The overall population size in the control and intervention arms are both estimated around 432.000 individuals.

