#### Entomological data

Entomological data for the assessment of secondary outcomes are collected in 12 clusters randomly selected from each arm (24 in total) and stratified by socio-economic status (medium versus low cost).

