### Monitoring *Aedes* population densities

The density of *Aedes aegypti* and *Ae. albopictus* populations will be monitored monthly throughout the study period using larval and adult collection methods in a sample of 12 clusters per arm. Larval surveys are carried out using a minimum of 40 ovitraps per cluster. Each ovitrap consists of a 250-ml cylindrical, black plastic container (7.5 cm diameter, 9.0 cm height, 300 ml volume) filled with tap water to a depth of 5.5 cm and is equipped with a removable oviposition paddle made from a thin strip of brown hardboard (10 cm × 2.5 cm × 0.3 cm). Larval surveys start 5 weeks before the start of the intervention to measure the baseline density. Ovitraps are positioned randomly in spaces with minimum human, physical, and environmental disturbance: (a) in the semi-indoor environment—defined as the area outside of the housing units but still sheltered by the roof (e.g. shared corridor and stairway), (b) in partially or totally shaded outdoor areas (e.g. near bushes, small plants, and temporary structures), and (c) indoor (under the sofa, dining table, sink, bed, working / study desk) only in the apartments of those who volunteer to have them.

To determine the OI, all ovitraps are collected once a week and replaced by new ones with fresh tap water and egg-free oviposition paddles. The collected ovitraps are brought back to the IMR laboratory (Kuala Lumpur) for further processing. Ovitrap contents and oviposition paddles are transferred into plastic containers and labelled with the name of the cluster and date of collection. Larvae emerged from the eggs laid in the ovitraps undergo species identification [30, 31] using a compound microscope (Nikon Eclipse® E100, Japan).

To determine the CI, a minimum of 20 suspected mosquito breeding containers within 50 m radius of the study cluster are examined once a month in each cluster. Larval samples from the positive containers are collected in a sample bottle and brought back for identification. The larvae are allowed to emerge into adults for morphological identification.

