To assess auto-dissemination efficacy of the ADDs, water samples of nearby containers are assessed for pyriproxyfen content. The *Aedes*-positive samples from natural containers collected for the CI (as explained above) are used to monitor larval development. Per 10 ml water sample collected, one susceptible strain larvae (L_3_, *Aedes aegypti*) is added to the water. Emergence of adults is monitored every day until all larvae have emerged or died. Significant reductions in adult mosquito emergence rates (i.e. high rates of larval/pupal mortality) in the intervention cluster samples compared to the control cluster samples is indicative of pyriproxyfen autodissemination from the ADDs.

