### Secondary outcome

The main secondary outcome will be the OI. The latter will be estimated over the baseline and intervention period in the 24 clusters selected for entomological monitoring. To quantify the effect of the interventions on the proportion of positive ovitraps, a modified ordinary least squares regression model using a robust standard error estimator will be implemented [21]. Using this model, the effect of the interventions will be quantified by the estimation of a difference of risk with its 95% confidence interval. This analysis will be carried out for both species overall and for each of the two species of mosquito separately.

Larval count per ovitrap (LI) will be estimated in the 24 clusters selected for entomological monitoring over the baseline and intervention period. A negative binomial regression will be used with the number of larvae as the response variable. The analysis will be adjusted by the baseline measurement of the outcome. Using this model, the effect of the interventions will be quantified by the estimation of a ratio of means with its 95% confidence interval. This analysis will be carried out for both species overall and for each of the two species of mosquito separately if possible.

The adult population will be estimated by counting the number of adult female *Aedes* mosquitoes collected with sticky ovitraps during the study. The total number of adult females will be divided by the number of sticky ovitraps used to obtain the mean number of adult females.

The emergence rate, defined as the proportion of larvae that emerge as adult mosquitoes, will be estimated in each arm and compared between the two arms using the chi-squared test or the Fisher exact test. This analysis will be carried out for both mosquito species combined and for each species separately.

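### The emergence-rate test treats individual larvae as independent, although they come from shared water samples in only 12 randomised clusters per arm

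*Protocol article*

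**What the plan says.** Trial design makes the locality the unit of randomisation: "a cluster is defined as a locality, i.e. one residential area composed of neighbouring buildings". Entomological data limits entomological follow-up to 24 clusters, 12 per arm, stratified by housing level.

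Secondary outcome defines the measure and the test: "The emergence rate, defined as the proportion of larvae that emerge as adult mosquitoes, will be estimated in each arm", and then "compared between the two arms using the chi-squared test or the Fisher exact test". No cluster-level or cluster-adjusted form of the test is named.

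Two other sections describe where larvae for an emergence test come from. Monitoring Aedes population densities says that "a minimum of 20 suspected mosquito breeding containers within 50 m radius of the study cluster are examined once a month in each cluster". Monitoring quality of TORS and ADDs post-application uses the Aedes-positive samples from those containers and states: "Per 10 ml water sample collected, one susceptible strain larvae (L_3_, *Aedes aegypti*) is added to the water". It then gives the reading of the result: "Significant reductions in adult mosquito emergence rates (i.e. high rates of larval/pupal mortality) in the intervention cluster samples compared to the control cluster samples" is taken as indicative of auto-dissemination from the devices.

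**The concern.** A chi-squared or Fisher test on larvae pooled by arm takes its variance from the number of larvae. The design supplies only 12 independent units per arm. Larvae placed in one water sample share that water. Samples from one locality share its containers and its local vector control. The same localities are surveyed month after month.

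Correlation is plausible even if auto-dissemination does nothing. Routine larviciding continues in both arms and is triggered by reported cases (Interventions), so larvicide in natural containers can differ between localities for reasons unrelated to the devices.

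At stake is the credibility of the field check on one of the three intervention components. If the p-value is too small, chance differences between localities may be read as evidence that pyriproxyfen reached surrounding breeding sites.

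**Working it through.** **No figure to reproduce.** The article gives no error rate, power or sample size for the emergence rate.

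**Inputs from the article.** There are 12 clusters per arm. At least 20 containers per cluster are examined monthly, and only Aedes-positive ones are used. One larva is added per 10 ml of sample. The two-sided 5% level is stated for the primary outcome only and is assumed here for the emergence test.

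**Inputs assumed.** Larvae per cluster, m, and the ICC. Neither can be derived. Two years of monthly surveys give at least 20 × 24 = 480 container examinations per cluster, but the share that is positive and the sample volume are not stated.

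**Formula.** With equal cluster sizes, the design effect is DE = 1 + (m − 1) × ICC. The unadjusted test rejects a true null with probability 2 × [1 − Φ(1.96/√DE)].

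- m = 10, ICC 0.01: DE = 1 + 9 × 0.01 = 1.09; 1.96/√1.09 = 1.88; rate 6.0%.
- m = 25, ICC 0.01: DE = 1 + 24 × 0.01 = 1.24; 1.96/√1.24 = 1.76; rate 7.8%.
- m = 25, ICC 0.05: DE = 1 + 24 × 0.05 = 2.20; 1.96/√2.20 = 1.32; rate 18.6%.
- m = 100, ICC 0.05: DE = 1 + 99 × 0.05 = 5.95; 1.96/√5.95 = 0.80; rate 42.2%.

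Type I error over a wider grid (nominal 5%):

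| Larvae per cluster | ICC 0.01 | ICC 0.05 | ICC 0.10 |
|---|---|---|---|
| 10 | 6.0% | 10.4% | 15.5% |
| 25 | 7.8% | 18.6% | 28.8% |
| 100 | 16.5% | 42.2% | 55.3% |

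**Check by simulation.** The simulation was beta-binomial, with 12 clusters per arm, an assumed 80% emergence in both arms and 4,000 runs (Fisher on 800). At ICC 0.05 the chi-squared test rejected in 18.7% of runs (m = 25) and 42.0% (m = 100). Fisher's test rejected in 16.9% and 39.2%, so it is no remedy.

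**After the fix.** In the same simulations a t-test on the 12 cluster proportions per arm rejected in 4.9 to 6.0% of runs across all settings tried.

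**Direction.** The article's criterion concerns reductions only. Under a symmetric null about half of the two-sided rejections favour the intervention, so false signals of auto-dissemination would be about 18.6/2 = 9.3% and 42.2/2 = 21.1% in the two ICC 0.05 settings, against a nominal 2.5%.

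**The case against.** The fair case against has four parts.

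- **Size is unknown.** With few larvae and an ICC of 0.01, the error is only 6 to 8%. This stands. A reader might infer that the rate must be several times 5%, but the article gives neither quantity needed to say so.
- **The measure is supportive.** Emergence is not in the list of secondary outcomes under Outcomes. It is described under post-application quality monitoring, and a significant reduction is called indicative, not conclusive. The primary dengue analysis is separate, and the ovitrap index has a robust standard error. This stands and lowers the priority.
- **The link between sections is inferred.** The monitoring section adds susceptible-strain *Aedes aegypti* larvae only, whereas Secondary outcome plans emergence analyses for both species. The article does not show that they are one dataset. This weakens the link to the auto-dissemination criterion, but not the objection to the test, which is applied between arms of a cluster-randomised trial.
- **The article is condensed.** Detail may sit in the full protocol or analysis plan. That would excuse silence, but here the text names the test.

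A reader might also extend the criticism to the larval count, where "A negative binomial regression will be used with the number of larvae as the response variable". The article does not support that. It does not state whether a record is a trap, a trap-week or a cluster total, nor does it exclude a cluster term. Outcomes defines the larval index as a ratio of totals. With one total per cluster, the dispersion parameter absorbs between-cluster variation, and simulated type I error was 4 to 11%. The unit of record is a detail that an article may leave to the fuller documents.

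**Conclusion.** The emergence-rate test is wrong as written. It counts larvae as independent in a design with 12 independent units per arm, and any positive within-cluster correlation pushes the false-positive rate above 5%.

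The size is conditional. It runs from about 6 to 8% (10 to 25 larvae per cluster, ICC 0.01), through 19% (25 larvae, ICC 0.05), to 42% (100 larvae, ICC 0.05). These figures rest on assumed larval numbers and ICCs, equal cluster sizes and a 5% two-sided level.

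The consequence is confined to a secondary, mechanistic comparison. It should be corrected before analysis, but it does not threaten the trial's main conclusion. Nothing here shows an error in the larval-count model.

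**What to change.** Replace the chi-squared or Fisher test with one of the following.

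- **Cluster-level comparison.** Pool each cluster's samples over the months into one emergence proportion. Compare the 24 values by a t-test or permutation test stratified by housing level. State how a cluster with no positive container is handled.
- **Mixed model.** Use logistic regression with random effects for cluster and container and small-sample degrees of freedom. This needs a container or sample identifier, which the article does not confirm is recorded.

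The first option needs no new data: containers are surveyed cluster by cluster, and Data management describes a common cluster identifier. The cost is a change of wording, a different SAS procedure and wider confidence intervals. By the design effects above, intervals widen by about √2.20 = 1.48 times (25 larvae, ICC 0.05) or √5.95 = 2.44 times (100 larvae, ICC 0.05).

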### Methods in analysis to handle protocol non-adherence and any statistical methods to handle missing data

The main analysis will be by intention to treat. The clusters will be analysed in their randomization arm. As explained above, the primary outcome is provided by the e-Dengue system and will be consequently available for the overall included clusters during the study period. A secondary per protocol analysis will be carried out excluding the clusters with any major deviations to the protocol. Major deviations will be defined by the technical committee (trial governance members) during the data review.

### Trial governance

Implementation of the field work is coordinated by IMR (Malaysia). The Malaysian Ministry of Health provide technical expertise and is in charge of dengue data extraction from the e-Dengue database. The Departments of Epidemiology and Public Health and of Biostatistics (Claude Bernard University and Hospices Civils de Lyon-France) host the project leader and are responsible for statistical analyses. The trial is governed by a technical committee composed of academic/private partnership with skills and knowledge in the epidemiology of infectious disease in particular vector-borne diseases, entomology, new vector control technologies, policy makers, and statistics. The committee defines the study design, review available data, and make decisions on trial conduct.

### Adverse event reporting and harms

The product for spraying outdoor walls is already registered in Malaysia and has been in use for vector control management. Both bio-actives of ADDs have short half-lives and are classified as low risk for non-target organisms. However, instructions about precautionary measures to be taken before and after the intervention are provided in the posters (supplementary material appendix 2) and during community engagement meetings. In addition, a dedicated phone number is provided by the research team to be contacted in the case of an event which might be linked to the interventions. We do not plan to set up a data monitoring committee for the purpose of this cRCT. The trial interventions do not include drugs. On ethical review in Malaysia, the study was assessed as no more than minimal risk.

### Plans for communicating important protocol amendments to relevant parties

Any modification in the protocol that significantly affects the scope or the scientific quality of the investigation will be submitted to the ethical committee with an amendment containing a verbatim description of the changes.

### Dissemination plans

The results of the trial will be disseminated through international scientific conferences and submitted to highly ranked peer-reviewed journals for publication. The findings will also be shared with regional, national, and international stakeholders and partners. Reporting will follow the guidelines in the Consolidated Standards of Reporting Trials (CONSORT) Statement [37]. Authorship will follow guidelines established by the International Committee of Medical Journal Editors (http://www.icmje.org/) which require substantive contributions to the design, conduct, interpretation, and reporting of a trial.

## Discussion

In the absence of vaccines and therapeutics, efficient, sustainable, and cost-effective vector control programmes are considered the principal method of protection against vector-borne diseases. New vector control technologies, prototypes, or products such as spatial repellents, ADDs, sterile insect techniques, and *Wolbachia* are currently under investigation by the Vector Control Advisory Group VCAG-WHO [38]. However, the epidemiological evidence of their impact on the incidence of vector-borne diseases is limited [39].

The iDEM trial aims to address this gap by measuring the effectiveness of a preventive IVM approach on the incidence of dengue. The well-known spatial heterogeneity of dengue incidence that leads to increased baseline inter-cluster variance and the inter-annual fluctuation of dengue epidemic have been taken into consideration during the study power calculation and by conducting the study over 2 years respectively. The results of the trial will provide valuable insights that could be of interest to national and international institutions involved in the control of dengue.

The vector control tools of the proposed IVM are relatively new and have been scientifically proven to be effective against vectors [3, 21, 40]. High bio-efficacy for K-Othrine® Polyzone used in semi-indoor areas with > 80% mortality for a period of almost 4 months has been reported in two studies carried out in Malaysia [21, 41]. These results suggest that TORS can potentially reduce the frequency of current insecticide applications, in particular in densely populated urban districts where coverage of indoor preventive measures is low. ADDs are currently registered and used in over 45 countries worldwide and were shown to be effective as auto-dissemination device under field conditions [21, 40].

The choice of RCT was based on the WHO guideline that considers this type of trial as level 1 of the hierarchy of study designs that is sufficiently robust to generate evidence on the efficacy and public health value of vector control products [12]. The cluster rather than individual-based RCT is well adapted to assess organizational and behavioural interventions, health promotion programs, or interventions that are usually implemented at the level of health organizational units or geographical areas. Although such design requires large sample size, it reduces contamination between those assigned to the intervention or control arm. The large scale cRCT described in this protocol is unique in its approach. It combines two relatively new control tools that complement each other by targeting both larval and adult stages of the mosquito’s life cycle. Using this combination, the TORS method will potentially reduce the infective adult mosquito while the ADDs will help to sustain the mosquito population below the threshold as described in the Malaysian Ministry of Health guideline [42]. This is further complemented by extensive public engagement activities to make the public better aware of the problems and solutions, encouraging a behavioural change. This could potentially increase the efficacy of vector control programmes and decrease dengue incidence.

The study area is suitable for the proposed trial because Malaysia is one of the Asian countries hardest hit by dengue, with all its current 32.6 million inhabitants at risk. The country has appropriate infrastructure (expertise in vector control management, strong social mobilization capacities, and existence of surveillance systems) that facilitates the successful implementation of such large-scale trials. The WHO-IVM approach [13] underlines the importance of strengthening communication among different healthcare bodies such as policy-makers and vector-borne disease programme managers for the implementation of mosquito control strategies. The trial is, therefore, carried out in close collaboration with the Malaysian Ministry of Health, enabling local support and continuity of the proposed IVM approach if promising results are observed.

The trial is designed to measure the reduction in the incidence of dengue in the intervention relative to the control areas using incidence data extracted from the national e-Dengue surveillance system. Although passive dengue surveillance in endemic countries is essential for timely detection and containment of outbreaks, it is subject to under-ascertainment (cases not being diagnosed) and under-reporting (cases being diagnosed but not included in surveillance data). In Malaysia, failure to report leads to penalties for medical doctors. This is therefore likely to reduce the under-reporting, in particular for symptomatic dengue cases. Imperfection of the dengue diagnosis tests is another concern [43]. The use of combined IgM and NS1 detection into one test in Malaysia allows for high sensitivity during both the early (NS1) and late (IgM) phases of the disease, thus improving the overall test performance. Only cases with positive RDT test and fulfilling the international clinical criteria (ICD10: A90, A91) are registered in the e-Dengue surveillance system, thereby improving the specificity of the system [23].

One possible source of bias is that due to the nature of the intervention, blinding was not feasible. A feeling of protection provided by the intervention could potentially affect health-seeking behaviour in case of a febrile episode or to a lesser extent to the use of other preventive measures. The latter reasoning has been suggested as an explanation in a recent study that evaluated the impact of insecticide treated curtains on dengue virus transmission [44]. Another concern is the continued compliance of participating clusters and their collaboration with the field workers during the intervention cycles to remove bulky objects from the corridors at the time of TORS spraying. Public trust in the Malaysian Ministry of Health, responsible for routine dengue prevention and control, and representing the main coordinator of the present intervention together with continuous dialogue with the community by providing information about the programme is expected to alleviate this issue. The routine vector control activities, which clearly are not being interrupted, will be monitored. However, these interventions would cause only an underestimation of the true effect of the proposed IVM strategy, relative to no action.

Even if efficient in the prevention and control of dengue, particularly for difficult to treat urban setting, a vector control programme such as the preventive IVM approach presented here can be scaled-up as a national programme if it is cost effective. Analysis of the cost-effectiveness of the proposed IVM strategy compared to the routine vector control activities is therefore a key parameter for its future adaptation as a national vector control program. Efforts are ongoing to secure the budget for the economic evaluation of our trial that will be conducted as an ancillary study of the present protocol.

In conclusion, a long-term residual effect of K-Othrine® Polyzone [21, 41], proven efficacy of ADDs [15, 16, 40], and relatively simple maintenance of both vector control methods would enable a sustainable preventative strategy instead of a responsive vector control. We expect that co-application of these vector control tools together with public cooperation could prove an invaluable vector control approach to reduce the burden of dengue. By regular communication with the residents, we hope to create local capabilities by transferring responsibilities (e.g. adding water to dried ADDs) and promote their participation (e.g. destruction of breeding sites) in national efforts to reduce the burden of dengue.

Considering the ongoing expansion of dengue burden in Malaysia, setting up proactive vector control strategies are critical. The results will be informative for a better understanding of effectiveness of proactive IVM approach in the control of dengue. Evidence from this trial may help justify investment in preventive IVM approaches as preferred to reactive case management strategies. It is conceivable that the result of this trial could be used in other locations with similar ecology or adapted to other *Aedes* borne diseases with same vector and process of transmission.

